
### Clinical outcomes

In addition to acceptability and feasibility endpoints, a number of clinical endpoints are measured at each follow-up time point. Although the trial is not powered to detect a meaningful difference in clinical endpoints, these data will provide important preliminary data for the design of a full-scale trial should feasibility criteria be met.*Proportion of children relapsing*. The proportion of children who relapse will be compared between study arms. Relapse to SAM will be defined as MUAC < 11.5 cm and/or WHZ < −3. Children who relapse to SAM will be re-admitted to the nutritional program. These children will continue to be monitored in the study. We will also assess the proportion of children who relapse to MAM by arm, defined as MUAC < 12.5 cm and/or WHZ < −2.*Time to detection of relapse*. Time from enrollment to first relapse will be analyzed in both arms. The date of relapse will be defined as the earliest date the relapse was identified in the clinic, via a planned study visit or unscheduled clinic visit.*Anthropometric outcomes*. At all study visits, weight, height, and MUAC measurements will be collected. We will compare growth based on weight and height as well as anthropometric measures defined by weight-for-age *Z*-score (WAZ), height-for-age *Z*-score (HAZ), and WHZ, calculated based on 2006 WHO child growth guidelines [9].*Vital status*. Vital status is assessed at the 6-month visit, and children are classified as alive, died, or unknown. Families who do not return to the clinic for the 6-month study visit will be contacted via phone call and/or home visit to ascertain vital status.*Hospitalization*. At each study visit, caregivers will be asked about any health care sought for the child since their previous visit. Reasons for seeking health care, and if the child was hospitalized overnight, will be recorded. In addition, data from the clinics in which children are enrolled are extracted from clinic records, and hospital records are queried, and data recorded for any hospitalizations of children enrolled in the study. To facilitate linking children to clinic and hospital records, a unique study identification number is placed in each child’s government-issued health card (*carnet de santé*). Clinic and hospital staff are sensitized to record this information for children enrolled in the trial.

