## Background

Severe acute malnutrition (SAM) affects 19 million children every year, most of whom are in sub-Saharan Africa and South Asia [1]. SAM is defined as a mid-upper arm circumference (MUAC) of < 11.5 cm and/or weight-for-height *Z*-score (WHZ) < −3 among children aged 6 to 59 months. Uncomplicated SAM is treated on an outpatient basis, with children receiving a package of interventions including ready-to-use therapeutic food (RUTF), antibiotics, antiparasitics, and any missing vaccinations [2]. The major goal of these programs is to induce rapid, acute weight gain in children to improve the probability of survival during the acute episode. Children are followed weekly until nutritional recovery, typically for several weeks to months. While specific criteria for achieving recovery vary by country and context, children are typically considered to have recovered if they have met specific anthropometric thresholds, typically MUAC ≥ 12.5 cm and/or WHZ ≥ −2 with no edema, and the child has been in treatment for at least 4 weeks. Most interventions for SAM focus on improving the probability of nutritional recovery.

Relapse after recovery from SAM has been increasingly recognized as a contributor to poor outcomes. Evidence suggests a large degree of variation in the proportion of children who relapse after successful SAM treatment, with as many as 37% of successfully treated children relapsing up to 18 months after treatment [3]. Children with SAM with worse anthropometric deficits at program admission have worse outcomes compared to those with better anthropometric deficits [4]. Children who relapse with SAM are re-admitted to nutritional programs. Identifying children who have relapsed earlier may improve outcomes in these children.

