### Recruitment and eligibility criteria

Caregiver-child dyads are recruited based on nutritional program registers which record outcomes for all children who are treated as part of the outpatient nutritional program. Caregivers of children who have received outpatient treatment for SAM and who have recovered from their SAM episode are screened by a study nurse for eligibility in the present trial. Caregiver-child dyads are eligible to participate if the caregiver is at least 18 years of age, the child is between 6 and 59 months, the child has recovered from an episode of SAM per Burkinabè national guidelines (MUAC ≥ 12.5 cm and/or WHZ ≥ − 2, depending on which criterion the child was admitted to the nutritional program) in the past month, the family is planning to stay in the study area for 6 months to facilitate retention in the study, and with appropriate consent from the caregiver or guardian.

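### The relapse-to-SAM endpoint uses MUAC and WHZ only, so a child who returns with edema alone is not counted as relapsed to SAM, although the Background describes recovery as typically edema-free

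*Protocol article*

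**What the plan says.** In the Clinical outcomes section, the protocol article gives the endpoint rule in full: "Relapse to SAM will be defined as MUAC < 11.5 cm and/or WHZ < −3". The milder category follows: "We will also assess the proportion of children who relapse to MAM by arm, defined as MUAC < 12.5 cm and/or WHZ < −2". Neither rule mentions edema. Time to relapse is counted from enrollment to the first relapse, dated to when the clinic first detects it at a planned or unscheduled visit.

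Edema appears once in the article, in the Background, where children are described as recovered on thresholds that are "typically MUAC ≥ 12.5 cm and/or WHZ ≥ −2 with no edema". That sentence opens with a qualifier: "While specific criteria for achieving recovery vary by country and context".

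The definitions that the trial works with leave edema out. The Background states that "SAM is defined as a mid-upper arm circumference (MUAC) of < 11.5 cm and/or weight-for-height" Z-score below −3. The eligibility criterion for recovery is MUAC of at least 12.5 cm and/or WHZ of at least −2, "depending on which criterion the child was admitted to the nutritional program".

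On data capture, the Clinical outcomes section says: "At all study visits, weight, height, and MUAC measurements will be collected".

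Under Feasibility and acceptability outcomes, the relapse proportion over 6 months is to feed the sample size and the justification of a full-scale trial. A low value would be read as meaning that interventions against relapse are not needed.

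**The concern.** The Background describes leaving the state of malnutrition with an edema condition, and the endpoint defines returning to it without one. A child who returns with edema alone is not recovered as the Background describes recovery, yet has not relapsed to SAM under the endpoint.

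This is a rule that the article states in full, so it is not a detail left to a later analysis plan. If edema were not observed at the visit, no analysis plan could recover it afterwards.

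The relapse proportion is at stake because it informs whether a full trial is worth running and how large it should be. Time to relapse uses the same event definition. There is also a point specific to this intervention. Caregivers act on a red MUAC reading, so the full trial needs to know what share of relapses a tape cannot show. Relapses on WHZ alone will be visible in the data as defined. Relapses on edema alone will not.

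**Working it through.** The article gives no relapse rate, power calculation or edematous share, so there is no figure of its own to reproduce. The check has two parts.

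**1. Apply the written rules to a child who returns with edema.** The MUAC and WHZ values are illustrative.

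| Child with edema | SAM rule (MUAC < 11.5 or WHZ < −3) | MAM rule (MUAC < 12.5 or WHZ < −2) | Counted as |
|---|---|---|---|
| MUAC 12.6 cm, WHZ −1.9 | not met | not met | no relapse |
| MUAC 12.0 cm, WHZ −2.3 | not met | met | MAM only |
| MUAC 11.3 cm, any WHZ | met | met | SAM relapse |

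Only the first two rows are affected.

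**Direction.** The criteria are joined by and/or. Adding a further alternative can only enlarge the set of children who qualify, so leaving it out can only shrink that set. The relapse count therefore cannot be overstated by the omission. A child who shows edema first and crosses a MUAC or WHZ threshold later is given a later relapse date, and one who never crosses has no event.

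**2. Illustrate the size.**

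Inputs:
- N = 200 dyads (Sample size section).
- Counted relapses: 30, that is 15% of 200. This is an assumption.
- s, the share of all SAM relapses that show edema only: 2% to 10%. This is an assumption.

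Counted relapses = all relapses × (1 − s), so missed = 30 × s / (1 − s).
- s = 2%: 30 × 0.02 / 0.98 = 0.6 children, or 0.3 percentage points of 200.
- s = 10%: 30 × 0.10 / 0.90 = 3.3 children, or 1.7 percentage points of 200.

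A wider range takes the true relapse proportion from 10% (assumed) to 37%, the highest figure cited in the Background, with s from 0% to 10%. The shortfall is true proportion × s.
- s = 0%: no shortfall.
- 10% × 0.10 = 1.0 percentage point, or 2 of 200.
- 37% × 0.10 = 3.7 percentage points, or about 7 of 200.

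The 37% figure covers up to 18 months in other settings, so the last line is an extreme for a 6-month follow-up.

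For comparison, the sampling uncertainty of a 15% proportion in 200 children is ±1.96 × √(0.15 × 0.85 / 200) = ±4.9 percentage points, or about ±10 children.

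**The case against.** The strongest reply is that the protocol does not conflict with itself. The edema phrase is general Background text, hedged as typical and as varying between countries. The article's own definition of SAM, the eligibility criterion for recovery and the relapse endpoint all rest on MUAC and WHZ alone, and the SAM and relapse thresholds are identical. This stands. A reader might infer that the trial requires absence of edema for recovery and then contradicts itself at relapse. The text does not support that.

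Second, a reader might infer that edema is not recorded at all. The Participant timeline section introduces weight, height and MUAC as included among the anthropometric measurements, which is not an exhaustive list, and edema is a clinical sign rather than an anthropometric measurement. The article condenses protocol version 1.4, which is not shown and may provide for edema. This also stands. The point concerns the stated endpoint rule, not the visit form.

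Third, it is tempting to say that fluid retention turns the weight and WHZ outcomes in the wrong direction. An outcome is affected only if edema is present when that measurement is taken, and the documents give no basis for a size. This supports a sensitivity analysis, not a claim of bias.

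Fourth, the likely effect is small beside the sampling error, and no numeric relapse threshold is set that a few children could cross. That limits the importance of the point. It does not remove it, because the error runs one way and does not shrink with a larger sample if the definition is carried into the full trial.

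**Conclusion.** The point holds as a cheap improvement to the endpoint. As written, a child with edema alone is counted as not relapsed, or as relapsed to MAM only, so the relapse proportion can only be understated and relapse times can only be late or missing. This one-way statement applies to the proportion in each arm and overall. It does not say which way a difference between arms would move.

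Under the assumptions of 30 counted relapses and a 2–10% edema-only share, about 1 to 3 of 200 children are missed. Neither assumption comes from the documents, and the share could be close to zero in this population. The conclusion does not rest on a contradiction between operative definitions, and it does not extend to every edematous child, since those who also cross a SAM threshold are counted.

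**What to change.** Reconcile the Background, the Recruitment and eligibility criteria and the Clinical outcomes section on whether edema counts:

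- Add nutritional edema as a further criterion in the study's relapse-to-SAM endpoint.
- Record edema yes/no at each study visit, if this is not already done.
- Report edema-only relapses separately, so that the proportion on MUAC and WHZ alone remains available and the share that a tape cannot show is known.
- Repeat the weight-based analyses without measurements taken while edema was present.
- Use re-admissions to the nutritional program as a cross-check on relapse, not as a relapse criterion. Counting every re-admission would replace a measured endpoint with a program decision, which this point does not require.

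These changes concern the endpoint and data capture only, not how children are managed.

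The cost is one clause in the outcome definition and, where needed, one form field. The downside is timing: recruitment began on 1 December 2023, so visits completed before the change may lack the field and would rely on clinic records, which the study already extracts. The report should say how many visits this affects.

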### Feasibility and acceptability outcomes

The primary outcomes for the trial are focused on feasibility and acceptability. Feasibility endpoints focus on both the feasibility of conducting a large-scale trial that is powered for relevant clinical outcomes as well as feasibility of integration of caregiver screening into the existing health system. Acceptability focuses on acceptability of integration of caregiver screening from both the caregiver and clinic perspective.*Enrollment and follow-up*. We will assess the speed of enrollment and rate of refusal to enroll in the trial as an indicator of potential for enrollment in a full-scale trial. We will consider success to be enrollment of the target sample size in a 6-month period and refusal of < 10% of eligible participants. We will also assess follow-up at the 6-month primary endpoint visit and consider success to be retention of > 85% of participants at 6 months.Proportion of children who relapse. Assessment of the proportion of children who relapse over the 6-month period post-discharge will establish how frequently children relapse in this population, which will contribute to sample size calculations and justification for a full-scale trial. A low probability of relapse would indicate that interventions intended to reduce the risk of relapse are not warranted.Time to conduct MUAC training. To understand the additional burden on the existing healthcare system for training caregivers to screen for MUAC, the time training takes for each caregiver is measured during the enrollment visit. Extended time for training would be more difficult to implement in real-world nutritional programs. An acceptable time for training will be established via nutrition program interviews as part of the acceptability assessment, described below.*Accuracy of caregiver MUAC training*. At enrollment and 6 months, the accuracy of caregiver MUAC measurements against a gold standard (nutrition program staff) measure is collected. The caregiver and the nutrition program staff member each measure the MUAC of a child attending the clinic masked to each other’s measurements, categorized as “normal” (≥ 12.5 cm, green section of tape), “moderate acute malnutrition” (< 12.5 cm to ≥ 11.5 cm, yellow section of tape), or “severe acute malnutrition” (< 11.5 cm, red section of tape). Due to high levels of caregiver illiteracy, we will not collect numeric measurements. Concordance between color-based categories will be assessed to measure accuracy.*Adherence to the intervention*. Caregivers in the MUAC screening arm will be asked to report how often they screened their child at each follow-up visit. Infrequent caregiver screening would indicate that the intervention may not be acceptable or feasible. Caregivers are also asked to bring back the MUAC tapes at each visit, so the study team can confirm that they are still in possession of the caregiver and ensure that they are not damaged. Missing or damaged MUAC tapes are replaced and recorded.*Adherence to the follow-up schedule*. Standard of care in Burkina Faso includes monthly follow-up visits in the clinic to monitor for signs of relapse. By measuring how often children who have recovered return for scheduled follow-up in the standard of care arm, we aim to understand gaps in care. Low adherence to the follow-up schedule may suggest that additional interventions are needed, or a reduced follow-up schedule should be considered if relapse rates are low.*Caregiver acceptability*. Caregivers complete quantitative surveys related to their experiences screening children for relapse in the screening arm, including data on ease of use, frequency of screening, whether the MUAC tape was lost or stolen, and evaluation of caregiver-perceived importance of screening and whether this is a priority for them in relation to other demands in their lives. A subset of 20 randomly selected caregivers will be invited to participate in an in-depth individual qualitative interview, focusing on their experience with malnutrition screening, diagnosis, treatment, and relapse as well as their child’s general health, and their experiences related to screening. Interviews will be conducted by a study investigator with expertise in qualitative methods. Interviews will be transcribed, translated into English, and analyzed based on an inductive and deductive approach to identify themes guided by immersion crystallization.*Clinic acceptability*. Acceptability from the clinic perspective will be assessed via in-depth interviews with nutritional program staff and clinic leadership. These interviews will focus on the evaluation of MUAC training, ease of implementation, and general barriers perceived by the clinic in the delivery of outpatient treatment for SAM. As part of these interviews, we will evaluate the resources that were required to implement the screening intervention and what is acceptable for implementation from the clinic perspective, including personnel time and space and privacy for training.

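### Eligibility tests recovery only on the admission criterion, but relapse to MAM is met on either criterion, so some children can be enrolled already meeting the MAM relapse definition and be counted as relapsed without deteriorating

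*Protocol article*

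**What the plan says.** **Eligibility** (Recruitment and eligibility criteria). The requirement is that "the child has recovered from an episode of SAM per Burkinabè national guidelines", with MUAC at least 12.5 cm and/or WHZ at least −2, "depending on which criterion the child was admitted to the nutritional program) in the past month". A child admitted on one measure has to clear only that one, and a child admitted on both has to clear both. The listed criteria set no anthropometric threshold for the enrollment visit itself.

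**Relapse** (Clinical outcomes). Relapse to SAM is MUAC below 11.5 cm and/or WHZ below −3. For MAM: "We will also assess the proportion of children who relapse to MAM by arm, defined as MUAC" below 12.5 cm and/or WHZ below −2. Either measure is enough in both definitions.

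**Timing.** In the same section, "Time from enrollment to first relapse will be analyzed in both arms", and "The date of relapse will be defined as the earliest date the relapse was identified in the clinic", at a planned study visit or an unscheduled clinic visit. Clinical endpoints are said to be measured at the follow-up time points. The section on feasibility and acceptability outcomes uses a different window: "Assessment of the proportion of children who relapse over the 6-month period post-discharge". It says the result will inform the size and justification of a full-scale trial, and that a low relapse probability would argue against such interventions.

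**The concern.** A relapse proportion should count children who were out of the state and returned to it. The MAM cut-offs for relapse are the exact complement of those for recovery, but recovery looks at one measure and relapse at two. A child who never cleared the second measure enters the trial already in the outcome state.

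Three things are at stake. The MAM proportion mixes malnutrition already present with new relapse. The same non-relapse events enter both arms and dilute any contrast in MAM relapse. In any time-to-relapse analysis that uses the MAM definition, false events appear at the earliest visits. Randomization should balance these children between arms, but it does not correct the absolute proportion, and the absolute proportion is what a later trial would borrow.

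**Working it through.** There is no figure in the plan to reproduce. The 200 dyads were chosen on logistical grounds, without a power calculation. The check is a comparison of definitions, followed by arithmetic on assumed values.

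**1. Definitions side by side**

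| Admitted on | Must clear to be eligible | Example at enrollment | Meets MAM relapse? | Meets SAM relapse? |
|---|---|---|---|---|
| WHZ only | WHZ ≥ −2 | WHZ −1.8, MUAC 12.2 cm | Yes, on MUAC | No |
| MUAC only | MUAC ≥ 12.5 cm | MUAC 12.5 cm, WHZ −2.5 | Yes, on WHZ | No |
| Both | Both | MUAC 12.6 cm, WHZ −1.9 | No | No |

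The example values are illustrative. The first two rows need no deterioration after discharge.

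**2. Why SAM differs.** If both measures were taken at admission, a child admitted on MUAC alone had WHZ of at least −3, and a child admitted on WHZ alone had MUAC of at least 11.5 cm. Meeting SAM at enrollment then requires the other measure to have worsened during treatment, or a fall after discharge. A fall after discharge is a genuine post-discharge relapse.

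**3. Size for MAM.** Let q be the share already meeting the MAM definition at enrollment and still below the cut-off at follow-up. Let r be the risk of new MAM relapse among the others. Neither is in the article, so both are assumed.

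Observed = q + (1 − q)r; overstatement = q(1 − r). With r = 20%:

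- q = 5%: 0.05 + 0.95 × 0.20 = 24% (4 points too high)
- q = 15%: 0.15 + 0.85 × 0.20 = 32% (12 points)
- q = 25%: 0.25 + 0.75 × 0.20 = 40% (20 points)

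The overstatement is larger when r is lower. At q = 20% it is 0.20 × 0.90 = 18 points for r = 10%, and 0.20 × 0.63 = 12.6 points for r = 37%. The 37% is the highest relapse figure in the Background, there for up to 18 months.

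**4. Dilution between arms.** Suppose the intervention cut new MAM relapse by 25%, from 20% to 15% (assumed). With q = 15% left in both arms, the proportions are 32% and 0.15 + 0.85 × 0.15 = 27.75%. The apparent risk ratio is 27.75/32 = 0.87 instead of 0.75.

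**5. Illustration for a later trial.** This applies only if that trial took its control risk from the MAM proportion. Assume a 25% relative reduction, 80% power and two-sided 5%, and use the pooled-variance formula for two proportions:

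n per arm = [1.960 √(2p̄(1 − p̄)) + 0.842 √(p₁(1 − p₁) + p₂(1 − p₂))]² / (p₁ − p₂)²

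For 20% against 15%, p̄ = 0.175 and n = (1.053 + 0.451)² / 0.0025, which is 906 after rounding up.

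| Control risk used | n per arm | Power if the true contrast is 20% vs 15% |
|---|---|---|
| 20% (q = 0) | 906 | 80% |
| 24% (q = 5%) | 723 | 71% |
| 32% (q = 15%) | 494 | 54% |
| 40% (q = 25%) | 356 | 42% |

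**6. Time origin.** Recovery may precede enrollment by up to a month. A window that starts at discharge and a clock that starts at enrollment can therefore differ by up to a month for the same child.

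**The case against.** The strongest points on the other side are these.

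- **SAM is the main target.** The design aims at detecting relapsed SAM, re-admission follows SAM, and MAM relapse is an additional outcome. The article does not say that the MAM proportion will size or justify the full trial. This stands: the sample sizes above are an illustration.
- **A reader might infer that the SAM proportion is overstated too.** The definitions do not support that. The SAM cut-offs are not complementary to recovery, and a child who falls back between discharge and enrollment is a real relapse in the post-discharge window.
- **A reader might infer that relapse is recorded on day 0.** The article does not say so; it ties clinical endpoints to follow-up visits. This changes the date, not the count: a child still below the cut-off is counted at the first follow-up visit.
- **A reader might take the time-origin mismatch as further overstatement.** It does not point that way. Starting at enrollment can miss relapses between discharge and enrollment, which lowers the figure.
- **No decision is shown to change.** No numeric threshold for low relapse is given, and the abstract lists relapse among the clinical endpoints, not the primary feasibility endpoints, although the feasibility section describes it too. This stands and limits the severity.
- **Small q is within sampling error.** At 20% with 200 children the 95% half-width is 1.96 × √(0.20 × 0.80/200) = 5.5 points, more than the 4 points at q = 5%. That is fair, but bias does not average out, and at q = 15% it is 12 points.
- **The full protocol or analysis plan may hold a baseline rule.** It may. The point does not rest on that absence alone: the article itself states an eligibility rule and an outcome definition which, applied together, count children already in the state as relapsed.

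**Conclusion.** The point holds for relapse to MAM. Applied as written, the eligibility rule and the outcome definition let a child be counted as relapsed to MAM with no deterioration. The overstatement is q(1 − r), provided those children remain below the cut-off at follow-up. For assumed r = 20% and q = 5% to 25%, the article's method would give 24% to 40% where the new-relapse risk is 20%. The direction follows from the definitions; the size rests entirely on assumed q and r. The SAM proportion is likely little affected. The post-discharge window and the from-enrollment clock are a separate inconsistency that needs to be settled. Severity is moderate, because the outcome is secondary to SAM relapse, the arms should be balanced, and the problem can be corrected at analysis.

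**What to change.** 1. Report each child's enrollment status on both MUAC and WHZ, by arm and by admission criterion.
2. Count relapse to MAM only among children who do not meet that definition at enrollment. Report those who do as baseline prevalence. The restriction uses a measurement of status at entry, not one that assignment can affect, so it should not bias the comparison between arms.
3. For SAM, report any child meeting the definition at enrollment separately. Do not discard a fall after discharge from the post-discharge estimate.
4. State one time origin per estimate: enrollment for the between-arm comparison, and the recovery date for any estimate described as post-discharge, with children entering observation at enrollment.

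The cost is analysis wording. The planned anthropometric analyses already use a baseline measure, and the recovery date and admission criterion are needed to apply the eligibility rule. The downside is fewer children and fewer events in the MAM analysis. No visit, measurement or care procedure changes.
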